## 2 INTRODUCTION

In normal individuals, phosphate is primarily eliminated by the kidneys which effectively regulate phosphate balance and blood phosphate concentration. Thus, in patients with end stage renal disease (ESRD) there is a marked decrease in phosphorus excretion in the urine, leading to hyperphosphatemia[1] unless they decrease their phosphate intake or treated with phosphate-binding agents to prevent absorption. There are serious long-term consequences of hyperphosphatemia, including bone demineralization, nausea and weakness[2]. In response to hyperphosphatemia, there is increased production of parathyroid hormone (PTH), a condition known as secondary hyperparathyroidism. If not treated, secondary hyperparathyroidism may cause many adverse clinical outcomes, one of which is a form of bone disease referred to as renal osteodystrophy, which can lead to pain and may progress to pathological fractures and significant skeletal deformity. Secondary and subsequent tertiary hyperparathyroidism, hyperphosphatemia, and elevated calcium phosphate have also been associated with increased mortality and other non-bone-related sequelae associated with extra-osseous calcification. It has been shown that a high intake of dietary phosphorus in experimental renal failure worsens renal function [3, 4] and low phosphate intake arrests the progression of chronic renal failure [2-4]. Restriction of dietary phosphate is usually not sufficient to reverse the hyperphosphatemia in patients with ESRD, therefore these patients are traditionally treated with orally administered aluminum or calcium compounds that bind dietary phosphate and facilitate fecal elimination rather than intestinal absorption. A variety of phosphate-binding agents have been used clinically including aluminum salts, calcium salts, sevelamer hydrochloride or carbonate, and lanthanum carbonate. These agents are effective in phosphate binding, however, there are specific safety, tolerability or cost concerns with each. Long-term administration of aluminum salts is associated with bone toxicity (it appears to block calcium deposition in the bone matrix and may interfere with osteoblast function as well [5, 6]) damage to neurological functions, and other toxicities (it accumulates in the parathyroid glands and may interfere with the secretion of parathyroid hormone [PTH], contributing to low bone-turnover)[5-7]. This has led to calcium salts being the phosphate-binding agents of choice. However, use of such compounds can lead to hypercalcemia, with resulting metastatic calcification and organ dysfunction [8-12]. In the ESRD patient, this can be further compounded by vitamin D therapy, lack of a reliable route of calcium excretion, hyperparathyroidism, and calcium-containing dialysate.

Nephoxil (ferric citrate) is an oral, non-calcium iron-based phosphate-binding agent that was approved to the control of serum phosphorus levels in patients with chronic kidney disease on dialysis. The active ingredient of Nephoxil® capsule is pharmaceutical grade ferric citrate which has been approved as a phosphate binder in Taiwan, United States, Japan and European Union. The ferric iron from ferric citrate reacts with the phosphorus in the GI tract, precipitating phosphorus as ferric phosphate. The latter is insoluble and is excreted in the stool. This process inhibits the gastrointestinal absorption of phosphate and reduces its systemic availability thus reducing serum phosphorus level.

Previous clinical studies have demonstrated the ability of ferric citrate to manage serum phosphorus in subjects with ESRD on dialysis. In the Taiwan pivotal Study, which is a randomized, double-blind, fixed dose, placebo-controlled study, serum phosphorus shows notable decrease as soon as receiving 1 week of treatment in both 4 g/day and 6 g/day groups. At the end of the study, the mean decrease from baseline in serum phosphorus is from 6.95 to 4.69 mg/dL (-2.27 mg/dL) in the 6 g/day group, and 6.96 to 5.38 mg/dL (-1.60 mg/dL) in 4 g/day group. Both dose groups achieved statistical significance of P-value <0.001.

Ferric citrate has been administered to the ESRD patients from 1 g/day to up to 12 g/day, and the study duration was from 4 weeks to at least 52 weeks safety monitoring in previous clinical

programs. Across these clinical studies, ferric citrate demonstrated a consistent AE profile and safety profile. Based on the clinical experiences, the adverse events of ferric citrate are mostly associated to mild to moderate GI tract discomfort and among which discolored feces is the most common adverse reaction reported, followed by constipation, abdominal distension, diarrhea and abdominal pain. Although clinical studies conducted to date have demonstrated that ferric citrate has an acceptable risk-benefit profile, there is a need for information from real-world clinical practice to establish the long-term safety profile of ferric citrate in Asian/Chinese population.

### **3 STUDY OBJECTIVES**

The objectives of this study are to assess the long-term safety and effectiveness of ferric citrate for the treatment of hyperphosphatemia in patients with ESRD undergoing dialysis in the real world situation.

### **4 STUDY VARIABLES**

#### **4.1 Variables to Determine the Safety**

The safety assessment is to assess the safety profiles from baseline to the end-of-treatment (EOT). Safety profiles will be assessed by monitoring and recording the incidence of treatment-emergent adverse events (TEAEs) and serious TEAEs, whether related to study treatment or not, as determined by changes in clinical laboratory tests (i.e., hematological tests and biochemical tests, including iron panels), physical examinations, vital signs, standard 12-lead electrocardiogram and any other untoward medical events during the study period. All subjects who receive at least one dose of study medication will be evaluated for safety.

To ensure complete safety data collection, all AEs occurring after signing the Informed Consent form, including any pre-treatment and post-treatment periods required by the protocol, shall be recorded. TEAEs will be defined as adverse events (AEs) with an onset date on or after the first dose of study treatment. AEs with missing onset dates will be assumed to be treatment-emergent. The incidence of TEAEs (any TEAE, serious TEAEs, drug-related TEAEs, serious drug-related TEAEs, and TEAEs leading to treatment discontinuation, or death) will be summarized, respectively. If a TEAE is reported more than once by a subject during the study, the one with the greatest severity will be included in the summary tables. A TEAE will be considered drug-related if the Investigator indicates that the event is “possibly”, “probably”, or “definitely” related or if the relationship is missing.

The variables used to describe TEAEs are listed below:

- 1) Clinical laboratory tests will be recorded at every visit including essential examinations and optional examinations. Essential examinations consist of routine hospital examinations and study-mandatory examinations. The essential examinations will be performed and collected according to protocol schedule at every visit unless otherwise stated (i.e., serum aluminum performed at Visit 1 and EOT [Visit 13 or early termination]; iPTH performed at Visit 1, Visit 4, Visit 7, Visit 10, and EOT [Visit 13 or early termination]). Optional examinations, although not mandated, will be collected and assessed if results are available following routine practice.
- 2) Physical examination of all body systems will be performed at each visit including the Early Termination visit. Physical examination at Visit 1 will include measurement of height (cm/inches) without shoes. If any of the physical examination results at any visit is a clinically significant change from the first physical examination determined by the Investigator, that result should be documented as an AE.
- 3) Pulse rate (bpm), supine blood pressure (mmHg), body temperature and body weight are measured at all clinic visits.

- 4) Standard 12-lead ECGs will be taken at Baseline (Visit 1), and at Month 12 (Visit 13) or at the Early Termination visit. The ECGs will be read locally by the Investigator or qualified designated reader (signed/dated). The Investigator will confirm the computerized measurements of PR, QRS, QT, and QTcB intervals. Changes in ECG parameters will be relative to the measurements taken from the baseline visit (Visit 1) ECG. Consideration should also be given to performing an ECG if the subject should report any symptoms suspicious for cardiac events.
- 5) Any other treatment-emergent adverse events, including worsening of baseline diseases, will also be assessed at all clinic visits.

#### **4.2 Variables to Determine the Efficacy**

The efficacy assessment are to evaluate efficacy on serum phosphorus by assess of the time-course changes of serum phosphorus levels from baseline to the end-of-treatment and proportion of subjects achieved the target range of serum phosphorus ( $\geq 3.5$  mg/dL and  $\leq 5.5$  mg/dL) from baseline to the end-of-treatment

#### **4.3 Variables for Exploratory Endpoints**

The following parameters will be explored:

- Time-course changes of serum calcium and intact plasma parathyroid hormone (iPTH) level from baseline to EOT.
- Time-course changes of Iron-parameters from baseline to EOT
- Time-course changes of hemoglobin from baseline to EOT
- Changes in dose of IV iron and ESA.
- Treatment adherence

#### **4.4 Other Assessment Variables**

Demographic data (age, gender, height, weight and race) will be recorded at Visit 1 (Baseline visit).

Medical and concurrent conditions at the time of initiation will be recorded in the medical and procedure history part of CRF at Visit 1 (Baseline visit) including

- Diagnosis date of CKD
- History of hemodialysis at the earliest known data point
- Primary etiology including
  - Diabetes nephropathy
  - Hypertensive nephrosclerosis
  - Non-diabetic glomerular disease (e.g. Focal segmental glomerulosclerosis (FSGS), membrane)
  - Polycystic kidney disease
  - Tubulointerstitial disease
  - Others
- Any previous or ongoing medical history and procedures or surgeries that occurred within 3 years prior to the study drug administration
- PTx (parathyroidectomy) or PEIT (percutaneous ethanol injection therapy)
- Any known history of allergy / drug sensitivity

## **5 STUDY DESIGN**

### **5.1 Study Description**

This study is an open-label, prospective, long term observational Phase IV study to assess the safety and efficacy of ferric citrate in subjects with ESRD on dialysis.

Subjects who meet the eligibility criteria and provided informed consent will be enrolled to the observational study for up to 13 months. No wash-out period will be required despite prior use of any oral phosphate binders.

Throughout the duration of the observation, study drug will be allowed for dose titration, targeting individual subject's serum phosphorus levels in between 3.5 and 5.5 mg/dL. Examinations to collect safety and efficacy measurements will be performed primarily according to routine hospital practice, except study drugs and additional tests that are specifically required to the study will be provided by the Sponsor.

The key measures collected for the patients will include, but not limited to, demography, medical history, physical examinations, vital signs, 12-lead electrocardiograms (ECG), clinical laboratory tests and prior/concomitant medications use for the evaluation of adverse events and treatment effectiveness throughout the observation period.

The end of the study is defined as the date of the last visit of the last subject in the study.

## **5.2 Planned Number of Subjects and Sites**

It is planned to recruitment of 200 patients in order to complete at least 100 subjects at 5~10 centers in Taiwan.

## **6 SELECTION AND WITHDRAWAL OF SUBJECTS**

### **6.1 Inclusion Criteria**

To be eligible to participate in this study, all of the following criteria must be met:

1. Is  $\geq 18$  years of age on the day of signing informed consent or other age required by local regulation
2. Willing and able to provide written informed consent
3. ESRD patients who is undergoing hemodialysis 3 times per week and is considered necessary to receive medication for hyperphosphatemia by his/her treating physician
4. Serum ferritin  $< 1000$  ng/mL and transferrin saturation (TSAT)  $< 50\%$  at the Enrollment Visit
5. Women of child-bearing potential (WOCBP [defined as women  $\leq 50$  years of age with a history of amenorrhea for  $< 12$  months prior to study entry]) who is willing to use an effective form of contraception during study participation.

### **6.2 Exclusion Criteria**

Subjects are not permitted to enroll in the study if any of the following criteria is met:

1. Has any known contraindication to ferric citrate according to locally approved prescribing information, include but not limited to the following criteria:
  - i. Is allergic to ferric citrate
  - ii. Has hypophosphatemia
  - iii. Has hemochromatosis or iron overload syndromes
  - iv. Has active severe GI disorders
2. Has parathyroidectomy (PTx) or percutaneous ethanol injection therapy (PEIT) within 3 months prior to Enrollment Visit or serum calcium  $< 7$  mg/dL at the Enrollment Visit
3. Has participated in another interventional study for any investigational agent or device within 30 days prior to enrollment
4. Is currently pregnant or breastfeeding

5. Other unstable medical condition or psychiatric conditions that is considered unsuitable for this study per Investigator's clinical judgment

### **6.3 Withdrawal Criteria**

Subjects are free to withdraw from the study at any time, without prejudice to their continued care. A subject may be removed from the study at any time if any of the following events occurs:

- Subject request
- Treatment failure
- Investigator's discretion for the best interest of subject
- Intercurrent illness or medical event necessitating study drug discontinuation

If the subject withdraws, the final evaluations will be performed as completely as possible. A clear and concise reason for withdrawal should be recorded in the case report form (CRF). If the subject is withdrawn because of an AE, the subject should be followed until the AE resolves.

If a subject has serum phosphorous level  $>8.0$  mg/dL in two consecutive monthly visits, not due to subject-reported non-compliance, the subject will be considered a treatment failure and will discontinue from the study.

## **7 STUDY MEDICATIONS**

### **7.1 Initial Dose**

All subjects will be instructed to take study drug intact with meals or immediately after meals and should not be opened or grounded.

Dose administration for the study drug will be at the discretion of the treating physicians and according to individual subject's clinical condition. The initial doses to be administered at study entry are suggested below:

- If the subject was on prior phosphate binders at a dosage equivalent to  $< 4.5$  g/day of calcium-based phosphate binders before entering the study, the suggested initial dose of study drug will be started from 3 g/day (2 capsules/meal, 6 capsules/ day).
- If the subject was on prior phosphate binders at a dosage equivalent to  $\geq 4.5$  g/day of calcium-based phosphate binders before entering the study, the suggested initial dose of study drug will be started from 4.5 g/day (3 capsules/meal, 9 capsules/ day).

### **7.2 Dose Adjustments**

The dose will be adjusted to meet target goal for serum phosphorus of 3.5 to 5.5 mg/dL with a maximum dose of 12 g/ day. The suggested dose adjustments as outlined are to be considered as guidance for dose administration throughout the observation period, instead of mandated procedures. Dose may be adjusted by 1-2 g/day on a scheduled or unscheduled visit under the Investigator's discretion. Reasons for dose adjustments, interruption or resuming of study treatment should be recorded in the CRF.

### **7.3 Drug Accountability**

At each visit after study drug is dispensed, subjects must return all unused IP and empty IP containers. Drug accountability must be done in the subject's presence in order to obtain explanations regarding discrepancies in compliance with the dosing regimen. Drug accountability must be recorded on the Drug Accountability form.

All returned trial medication will be assessed in order to monitor the subject's compliance with the medication schedule. All findings will be documented. If a subject was found to be persistently noncompliant (defined as  $\leq 75\%$  or  $\geq 125\%$  compliant with dosing schedule), Sponsor, in conjunction with Investigator, will decide whether the subject shall be withdrawn from the trial.

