#### **8.2 Visit 2 to Visit 12 and Visit 14**

The monthly visits will follow individual Investigator's routine clinical practice for each subject. However, it is suggested the monthly visits to be scheduled at regular intervals throughout the study period, e.g. approximately every 30 days.

Procedures are to be performed from Visit 2 through Visit 12, and the follow-up visit 14 including record concomitant medications, perform physical examinations and obtain vital signs, check for

adverse events, perform clinical laboratory test results, accountability on returned drugs and compliance check, and study drug dispensing

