### **8.3 Visit 13: End-of-Treatment /Early Termination Visit**

Procedures are to be performed at EOT including record concomitant medications, perform physical examinations and obtain vital signs, check for adverse events, perform clinical laboratory tests, and return all study drugs and empty containers

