### **9.4 Analysis of endpoint**

Safety assessment: This to assess the safety profiles from baseline to the EOT. Safety profiles will only be assessed by monitoring and recording the incidence of treatment-emergent adverse events

(TEAEs) and serious TEAEs, whether related to study treatment or not, as determined by changes in clinical laboratory tests (i.e., hematological tests and biochemical tests, including iron panels), physical examinations, vital signs, standard 12-lead electrocardiogram and any other untoward medical events during the study period. All subjects who receive at least one dose of study medication will be evaluated for safety.

TEAEs are defined as adverse events with an onset date on or after the first dose of study treatment. AEs with missing onset dates will be assumed to be treatment-emergent. Incidence of TEAEs will be summarized by the number, percentage, severity, and suspected relationship to study drug according to system organ class and preferred term using the MedDRA coding system.

**Efficacy assessment:** This is to describe the effectiveness of ferric citrate for the control of serum phosphorus concentration and achievement rate of target phosphorus level throughout 12 months of treatment. Treated patients who had an efficacy assessment at least once will be included in the full analysis set.

- Time-course changes of serum phosphorus levels from baseline to the end-of-treatment will be summarized according to each available observation visits. Continuous variables will be presented as mean  $\pm$  standard deviation or median with interquartile range, as appropriate.
- Proportion of subjects achieved the target range of serum phosphorus ( $\geq 3.5$  mg/dL and  $\leq 5.5$  mg/dL) from baseline to the end-of-treatment will be tabulated or plotted, as appropriate.

**Exploratory endpoint:** The following parameters will be explored:

- Time-course change of serum calcium and intact plasma parathyroid hormone (iPTH): Serum calcium and iPTH will be summarized descriptively as observed values at baseline, at every observation point, and at EOT. Changes from baseline will be descriptively summarized at completion of Visit 4 (Month 3), Visit 7 (Month 6), at Visit 13 (Month 12), and at EOT (including early termination).

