- Time-course changes of iron-parameters from baseline to EOT: Serum iron, ferritin, TSAT, and TIBC will be summarized descriptively as observed values at baseline, every observation point, and EOT. Changes from baseline will be descriptively summarized at completion of Visit 4 (Month 3), Visit 7 (Month 6), at Visit 13 (Month 12), and at EOT (including early termination).
- Time-course changes of hemoglobin from baseline to EOT: Hemoglobin will be summarized descriptively as observed values at baseline, every observation point, and EOT. Changes from baseline will be descriptively summarized at completion of Visit 4 (Month 3), Visit 7 (Month 6), at Visit 13 (Month 12), and at EOT (including early termination).
- Changes in dose of IV iron and ESA from baseline to EOT: Dose of ESAs and intravenous iron preparations will be summarized descriptively at baseline, every observation point, and EOT.
- Treatment adherence: Dose of study drug dispensed and actually taken between each visit will be recorded. Proportion of the prescribed dose versus the dose actually taken at each time point will be calculated and summarized as percentages. Accumulated dose of individual subjects will be summarized by the end of treatment or at early termination.

Details will be specified in the statistical analysis plan (SAP).

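### Section 7.3 allows withdrawal from the trial for persistent noncompliance, so later-visit adherence and phosphorus summaries can be selected on adherence itself

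*Protocol*

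**What the plan says.** Section 7.3 sets the limits for noncompliance at 75% or less and 125% or more of the dosing schedule. For a subject who is persistently outside them it provides that "Sponsor, in conjunction with Investigator, will decide whether the subject shall be withdrawn from the trial". The withdrawal is from the trial, not only from study drug. The decision is discretionary, and no duration is given for what counts as persistent.

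The study aims to assess long-term safety and effectiveness "in patients with ESRD undergoing dialysis in the real world situation" (section 3). Section 4.3 lists "Treatment adherence" among the exploratory endpoints. The monthly visits include "accountability on returned drugs and compliance check" (section 8.2). Section 9.4 plans this adherence summary: "Proportion of the prescribed dose versus the dose actually taken at each time point will be calculated and summarized as percentages". For serum phosphorus, section 9.4 says that the time course "will be summarized according to each available observation visits". Section 9.7 rules out imputation and bases all statistics on the data actually available. Section 9.3 makes the whole analysis descriptive, with no hypothesis test.

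Section 6.3 lists the withdrawal grounds, and noncompliance is not named among them. Its rule on phosphorus above 8.0 mg/dL at two consecutive monthly visits carries a qualification: "not due to subject-reported non-compliance, the subject will be considered a treatment failure".

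**The concern.** Adherence is something this study sets out to describe. Section 7.3 lets observation end because of the value that adherence takes. Once a subject has left the trial, no scheduled monthly visit follows, so the later adherence and phosphorus values are never generated. With no imputation and only available data, the later-visit summaries then describe the subjects who remain, who have been selected partly on how they took the drug.

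This fits poorly with a real-world aim. Starting doses and titration steps are guidance at the physician's discretion (sections 7.1 and 7.2), and no comparison is tested whose sensitivity strict compliance might protect. An analysis plan can count and list the withdrawals, but it cannot recover visits that did not take place. The remedy therefore has to sit in the protocol.

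**Working it through.** **Plan's own figures.** The protocol gives no rate of persistent noncompliance and no rate of withdrawal for it, so there is no stated figure to reproduce for this point. The nearest is the completion rate in section 9.1: 125/168 = 74.4%, which applied to 200 subjects gives 200 × 0.744 = about 149 completers against the 100 required. That figure reproduces, and the exposure target does not depend on the section 7.3 option.

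**Inputs.** From the protocol: the 75% and 125% limits (7.3), and the visit schedule with Visit 13 as end of treatment (8.2, 8.3). Assumed: *w*, the share of would-be Month 12 subjects withdrawn from one limb, and *m*, the mean adherence of those who remain, taken to be compliant, at 90%, 95% or 100%.

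**Shift in the planned measure.** Let *a* be the mean adherence that the withdrawn subjects would have had at Month 12.

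- Mean without withdrawal: (1 − w)·m + w·a. Mean with withdrawal: m. Difference: w·(m − a).
- Low limb, a ≤ 75: the mean rises by at least w·(m − 75).
- High limb, a ≥ 125: the mean falls by at least w·(125 − m).

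| w (assumed) | Low limb, m = 90 / 95 / 100 | High limb, m = 90 / 95 / 100 |
|---|---|---|
| 5% | up ≥ 0.75 / 1.0 / 1.25 points | down ≥ 1.75 / 1.5 / 1.25 points |
| 10% | up ≥ 1.5 / 2.0 / 2.5 points | down ≥ 3.5 / 3.0 / 2.5 points |
| 20% | up ≥ 3.0 / 4.0 / 5.0 points | down ≥ 7.0 / 6.0 / 5.0 points |

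For example, with w = 10% and m = 90: 0.10 × (90 − 75) = 1.5 and 0.10 × (125 − 90) = 3.5. If the option is never used, w = 0 and nothing shifts. If both limbs are used, the two terms have opposite signs and the net direction is not determined.

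**Visits lost per subject.** Visits 2 to 13 are 12 monthly visits. Withdrawal at Visit 4 loses Visits 5 to 13, which is 9 of 12; at Visit 7 it loses 6 of 12; at Visit 10 it loses 3 of 12. Section 9.4 fixes change-from-baseline summaries for calcium, iPTH, iron parameters and hemoglobin at Visits 4, 7 and 13. Withdrawal at Visit 4 loses 2 of those 3, and withdrawal at Visits 7 to 12 loses 1 of 3. One early-termination evaluation remains in each case.

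**What is kept.** Data before withdrawal, including the low or high adherence that prompted it, stay in the earlier summaries. Section 6.3 asks for final evaluations and a recorded reason. Section 8.3 combines early termination with the end-of-treatment visit ("Procedures are to be performed at EOT including record concomitant medications") and has remaining drug returned. Section 9.4 summarises accumulated dose at early termination and includes early terminations in several end-of-treatment summaries. Adverse events are followed for about one month after drug is stopped (10.1), and serious events are reported until at least 30 days after (10.2).

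**The case against.** The strongest reply is that the clause is permissive. It calls for a case-by-case decision on persistent noncompliance only, and it may be used rarely or never. The affected endpoint is exploratory and descriptive, the reason for each withdrawal is recorded, and the analysis plan can report the number. Review of a subject who persistently takes 125% or more is also sensible for an iron-based drug with a 12 g/day ceiling and an iron-overload precaution (7.2, 7.5). All of this stands. It limits the importance of the point, but it does not supply the missing visits, and the safety purpose is met by reducing or stopping drug without ending observation for noncompliance as such.

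Three stronger readings are tempting and are not supported.

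- A reader might infer that full use of the option makes the noncompliant share at Month 12 zero. That does not follow. Persistence first established at Visit 12 or 13 still leaves Month 12 data, subjects outside the limits but not yet persistently so remain in the summaries, and persistence has no stated duration. The protocol also plans no such share; it plans percentages of prescribed dose taken.
- A reader might infer that 6.3 and 7.3 contradict each other. Section 6.3 only keeps high phosphorus caused by reported noncompliance from being labelled treatment failure. It does not say that the subject must stay in the trial, so review under 7.3 is compatible with it.
- A reader might infer a flattering bias in phosphorus control. The two limbs may act in opposite directions, and the protocol gives nothing from which to derive a sign or size.

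It is also fair to say that the change does not close every route, since 6.3 still lets an investigator withdraw a subject in that subject's interest. That is a different ground, and it should remain.

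**Conclusion.** The point holds as a modest design improvement. Any use of the section 7.3 option removes a subject from later-visit adherence and phosphorus summaries because of adherence, in a study whose aim is to describe real-world use, and the analysis cannot restore those visits. The size is unknown. The 10% illustration (a rise of at least 1.5 to 2.5 points, or a fall of at least 2.5 to 3.5 points, in mean Month 12 adherence) rests on the assumed share withdrawn, on all withdrawals coming from one limb, and on an assumed mean of 90% to 100% among compliant subjects. No phosphorus shift is claimed. The primary incidence of treatment-emergent adverse events is largely preserved, because events before withdrawal and for about a month after stopping drug are still collected. The point merits consideration and does not threaten the study's main conclusions.

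**What to change.** In section 7.3, replace the withdrawal sentence with:

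> Persistent noncompliance and its reason are recorded in the CRF; noncompliance alone is not a reason for withdrawal from the trial, and subjects still prescribed study drug continue scheduled visits. The treating physician may reduce or stop study drug for safety (for example at ≥125%); if it is stopped permanently, the EOT and 1-month follow-up visits are performed.

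Leave the section 6.3 grounds unchanged, and add no collection of off-treatment results beyond those visits.

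The cost is a protocol amendment with the approvals in section 12.4, and payment for the study-mandatory tests (section 13) at visits that are already in the schedule but would otherwise be lost. The downside for the sponsor is that adherence and phosphorus figures may look slightly less favourable.
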